**Figure 1 F1:**
[figure not shown]
Study approach for screening, enrolment and management of sick infants. *Signs of Possible Serious Bacterial Infection (PSBI): convulsions, not able to feed at all, stopped feeding well, severe chest indrawing, body temperature ≥38°C, body temperature <35.5°C, movement only when stimulated, no movement at all, fast breathing in <7 days. **^†^**International Standard Randomised Controlled Trial Number (ISRCTN) Registry [29]. CSI – clinical severe infection, IV – intravenous, IM – intramuscular

**Table 2 T2:** Implementation Strategy for Intervention and Control Arms

Activity	What	Who	When	Where	How
Case identification	Detection of cases	Screening, Enrolment and Randomisation Team with hospital staff	The sick young infant is brought by the family for consultation	OPD or general or paediatric emergency department of the hospital	Clinical assessment
Screening, randomisation and enrolment	Detection of eligible cases	Screening, Enrolment and Randomisation team	The young infant is seen by the hospital staff and the study staff	OPD or general or paediatric emergency department of the hospital	Clinical assessment, administering informed consent, randomisation and enrolment
Intervention arm (outpatient): treatment provision	Injection gentamicin and oral amoxicillin	Hospital / study staff and mothers	After enrolment and consent	First doses and subsequent injectable doses are given at the place of enrolment and the remaining oral doses are given at home by the mother / caregiver	Practical demonstration of giving the first dose in front of the mother / caregiver
Control arm (inpatient): treatment provision	Injection gentamicin and injection ampicillin	Hospital / study staff	After enrolment and consent	Hospital	Giving injectable therapy
Treatment documentation	Follow-up for treatment documentation	Treatment Documentation Team	2, 4, 8 post-randomisation	Intervention arm: patients' homes and OPD	Intervention arm: asking mothers and checking medicine bottles
				Control arm: hospital where the patient is admitted	Control arm: hospital inpatient treatment records
Supervision	Sub-sample on follow-up days for quality assurance	Study supervisor	2, 4, 8 and 15 post-randomisation	Intervention arm: patients’ homes and OPD	Verification and substantiating assessment
				Control arm: hospital where the patient is admitted and the patients’ home after discharge	
Outcome assessment	Outcome assessment	Independent Outcome Assessment Team	Day 2, 4, 8, 15 post-randomisation and if the patient deteriorated in between	Intervention arm: patients’ homes or a hospital if the patient was admitted	Clinical assessment and filling outcome assessment form
				Control arm: hospital where the patient is admitted and at home after discharge	

*OPD – outpatient department

### Randomisation to treatment arms

Participants will be individually allocated to inpatient or outpatient treatment with a block randomisation scheme. WHO staff in Geneva not associated with site work prepared the randomisation list in blocks of 2, 4, 6 and 8 and shared it with the Regional Triangle Institute (RTI), the study Data Coordination Centre (DCC). Allocation concealment was ensured using QR randomisation codes. Randomisation was in a 1:1 ratio. RTI produced a list of encrypted QR codes and has these printed on labels based on the randomisation scheme for each site and study. RTI transmitted the printed QR code with blue colour labels to the sites. There will be three labels per infant: one each for the log register, patient card, and hospital file or outpatient department (OPD) slip.

Each hospital within the site will have a single set of QR codes that all screening and enrolment team members will use, even if the screening and enrolment are taking place in different locations within the hospital. After determining eligibility, the data collector will take the QR code label next in the numeric sequence from the list at their facility and scan this to obtain the randomisation number.

### Sample size

The sample size was calculated to test both the superiority and noninferiority hypotheses. The target enrolment is 7000 young infants (3500 in each study arm) with low-mortality risk signs. This sample size will allow us to meet the superiority and inferiority targets given in **Table 3**.

**Table 3 T3:** Sample size calculation for the trial design

Trial design	% poor clinical outcome in the control arm [6,7]	% poor clinical outcome in the interventional arm	Power	% lower outcome or noninferiority margin	Sample size needed
Superiority	6.0	4.0	90%	30	6270
Superiority	6.0	4.5	80%	25	6938
Noninferiority	6.0	6.0	90%	1.8	5966
Noninferiority	6.0	6.0	80%	1.5	6202

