### Data management

All study data will be collected on electronic case report form (CRF). Each site will collect data using Android-enabled devices using the PSBI data management system developed on the Tangerine software platform (http://www.tangerinecentral.org/ and https://docs.tangerinecentral.org/). Quality control will be performed on-site: each research team member will be responsible for data quality checks and ensuring that all forms are correctly filled out. A central data repository will be created. All efforts will be made to minimise missing data. There will be no imputation of missing data. RTI will develop and support a common data management system in collaboration with WHO and site investigators, conduct statistical analysis and support data monitoring, and perform on-site monitoring visits to improve the quality of data. Standardised data collection tools will facilitate the study data to be entered directly into the electronic forms using laptops, notebooks, or other portable electronic equipment. While centralised, however, each site will also own and support the data collection system. The data management system will be maintained and managed locally at each site, with support, as needed, from RTI technical staff. RTI will develop a data monitoring plan in collaboration with the WHO and study investigators to provide regular reporting on data recruitment, adherence to the study protocol and other metrics deemed important. RTI will provide periodic additional reports as needed (i.e., in preparation for the DSMB or Steering Committee meetings) from the centralised monitoring.

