### Data analysis

Means and proportions of baseline characteristics by inpatient and outpatient groups will be presented. The primary analyses will be intention-to-treat to compare the risk of poor clinical outcomes between the intervention and control arms. Risk difference and the 95% confidence intervals will be presented to assess. Those who will be lost to follow-up and from whom consent would be withdrawn will not be included in the per-protocol analysis. The treatment outcomes between control and intervention groups will be compared, and the difference in the risk of poor clinical outcomes together with 95% confidence intervals, will be calculated. Secondary analyses will be performed to investigate the effect on secondary outcomes (predictors of poor outcomes); that is, univariate and multivariate regression analyses will be performed to identify predictors of poor clinical outcomes.

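### Table 3's non-inferiority rows imply a one-sided 5% test, but the only interval named for the analysis is a 95% confidence interval; read from that interval, 7000 infants fall short of both stated powers

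*Protocol article*

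**What the plan says.** All references are to the Methods of the protocol article.

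- **Sample size, total.** "The target enrolment is 7000 young infants (3500 in each study arm) with low-mortality risk signs". Of this total the text says: "This sample size will allow us to meet the superiority and inferiority targets given in" Table 3.
- **Table 3, non-inferiority.** The rows, read across as control rate, intervention rate, power, margin and total needed, are "Noninferiority 6.0 6.0 90% 1.8 5966" and "Noninferiority 6.0 6.0 80% 1.5 6202".
- **Table 3, superiority.** One row reads "Superiority 6.0 4.5 80% 25 6938". The other pairs 6.0% with 4.0%, a 30% reduction, 90% power and 6270 infants.
- **Alpha.** Neither the text nor the table gives an alpha or says whether a test is one- or two-sided.
- **Randomisation to treatment arms.** "Randomisation was in a 1:1 ratio".
- **Data analysis.** For the primary comparison, "the difference in the risk of poor clinical outcomes together with 95% confidence intervals, will be calculated". No 90% or one-sided interval appears anywhere, and the section does not mention non-inferiority.

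**The concern.** The Abstract and the Discussion pose the question as whether outpatient care is superior or, failing that, non-inferior. Non-inferiority is therefore the claim the trial falls back on if superiority is not shown. The power printed for it should belong to the test that will be used.

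The sample sizes in Table 3 show which error rate was used, even though none is printed. If that rate is more lenient than the one carried by the interval in Data analysis, the stated power is too high for the test a reader would expect. There is a second cost. With the deciding interval unsettled, a result that clears the margin on a 90% interval but not on a 95% interval could be called either way once the data are known.

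**Working it through.** **Inputs.** Event rates, margins, powers and totals come from Table 3; the 1:1 ratio comes from Randomisation; the 95% level comes from Data analysis. The margins are taken as absolute percentage points, which the document does not say but which reproduces the printed totals.

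**Formula.** With both arms at 6.0%, the variance term is 2 × 0.06 × 0.94 = 0.1128, and the number per arm is (z_alpha + z_power)² × 0.1128 / margin². Double it for the total.

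**1. Reproduce the non-inferiority rows at one-sided 5%.**
- Margin 0.018, 90% power: (1.645 + 1.282)² = 8.564; 8.564 × 0.1128 / 0.000324 = 2981.5 per arm; total 5963 (printed 5966).
- Margin 0.015, 80% power: (1.645 + 0.842)² = 6.183; 6.183 × 0.1128 / 0.000225 = 3099.5 per arm; total 6199 (printed 6202).

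Working backwards from the printed totals, the implied one-sided alpha is 0.0499 in both rows.

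**2. The same rows at one-sided 2.5%, the level of one limit of a two-sided 95% interval.**
- Margin 0.018: (1.960 + 1.282)² = 10.507; total 2 × 10.507 × 0.1128 / 0.000324 ≈ 7316.
- Margin 0.015: (1.960 + 0.842)² = 7.849; total 2 × 7.849 × 0.1128 / 0.000225 ≈ 7870.

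Neither matches the table. Both exceed 7000, by 316 and 870.

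**3. The superiority rows.** The standard two-proportion formula was used, with pooled variance under the null.
- 6.0% v 4.5%, 80% power: about 6939 at two-sided 5% (printed 6938), against about 5465 at one-sided 5%.
- 6.0% v 4.0%, 90% power: about 4987 at two-sided 5%, which does not match the printed 6270. At 4.2%, which is 6.0% less the stated 30%, it gives about 6274 (6268 with unpooled variance). The printed 4.0% looks like a rounding of 4.2%.

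The table thus carries 2.5% per tail for superiority and 5% for non-inferiority.

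**4. Power with 3500 per arm, 6.0% in both arms and no losses.** The standard error of the difference is √(0.1128 / 3500) = 0.005677, or 0.568 points. Power is Φ(margin / SE − z_alpha).

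| Margin | Stated power | One-sided 2.5% (95% CI) | One-sided 5% (90% CI) |
|---|---|---|---|
| 1.8 | 90% | Φ(3.171 − 1.960) = 88.7% | Φ(3.171 − 1.645) = 93.6% |
| 1.5 | 80% | Φ(2.642 − 1.960) = 75.2% | Φ(2.642 − 1.645) = 84.1% |

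**5. Where the choice of interval would decide the result.** The half-widths are 1.960 × 0.568 = 1.11 points (95%) and 1.645 × 0.568 = 0.93 points (90%). With the 1.5-point margin, an observed excess risk between about 0.39 points (1.5 − 1.11) and 0.57 points (1.5 − 0.93) would be non-inferior on the 90% interval and not on the 95% interval. With the 1.8-point margin the band is about 0.69 to 0.87 points.

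**The case against.** The strongest reply is that nothing printed is false on its own terms. No alpha is given, and no sentence says that non-inferiority will be declared from the upper limit of a two-sided 95% interval. Two rows landing within three infants of the one-sided 5% result suggest a deliberate design level, not a slip. At that level 7000 infants give 93.6% and 84.1%, and the claim in the Sample size section is true. The decision rule may also sit in a full protocol or analysis plan that is not shown.

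Much of this stands. The one-sided 5% level is inferred, and the fault is a conflict between two sections, not a miscalculation. It does not remove the point. The article prints enough to be checked, it names only one interval, and under that interval the claim about 7000 fails for both non-inferiority rows. If one-sided 5% was meant, the 95% interval is not the deciding one and the article should say so.

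Two stronger readings are tempting but unsupported.

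- A reader might infer that the trial is too small and must enrol more. Under the 95% interval the 1.8-point row is only about one point of power short. The rows are alternative scenarios, and the document names none of the margins as primary.
- A reader might also combine the slack of 62 infants in the tightest superiority row (7000 − 6938) with the statement "There will be no imputation of missing data" and conclude that losses were overlooked. A loss allowance is something an article commonly leaves to the full protocol. The Follow-up section describes retention measures, and the Withdrawal section keeps withdrawn infants in the intention-to-treat analysis. The document does not support a finding there.

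**Conclusion.** The point holds as an inconsistency between Sample size and Data analysis. The statement that 7000 infants meet the Table 3 targets is not true under the only interval the document names. The effect is uneven: about 1.3 points of power for the 1.8-point margin (88.7% against 90%), which is minor, and about 5 points for the 1.5-point margin (75.2% against 80%), which is material.

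This rests on four assumptions: margins in absolute percentage points, a true rate of 6.0% in both arms, no losses, and non-inferiority judged from the upper limit of a two-sided 95% interval. If the last is replaced by a one-sided 5% rule, the targets are met and what remains is that the rule is unstated and at odds with the interval that is named.

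**What to change.** Reconcile the two sections before any outcome data are seen.

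- **Preferred.** State in Data analysis that non-inferiority is judged from the two-sided 95% interval. Restate the non-inferiority rows at one-sided 2.5%: about 7316 infants for the 1.8-point margin at 90% power and about 7870 for the 1.5-point margin at 80%, or equivalently about 89% and 75% power at 7000. Amend the sentence claiming that 7000 meets every target.
- **Alternative.** State explicitly that non-inferiority is judged at one-sided 5%, from a 90% interval, and report about 94% and 84% power at 7000.

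In either case print the alpha and sidedness for every row of Table 3, and correct or explain the 4.0% in the 30% superiority row.

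The cost is a revised table and a sentence or two. Enrolment need not change. Under the preferred option the price is a less favourable power figure, chiefly for the 1.5-point margin.

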**Methods:**

This is a protocol for a multicentre, individually randomised, open-label trial that will be conducted in seven sites in six countries Bangladesh, Ethiopia, India (two sites), Nigeria, Pakistan and Tanzania. All sites will use this common protocol with the same study design, inclusion of participants, intervention, comparison, and outcomes, as well as quality control and analysis procedures to contribute to the overall sample size. All young infants (age <60 days) presenting at study hospitals with any single low-mortality risk sign (high body temperature ≥38°C, severe chest indrawing, or fast breathing of ≥60 breaths per minute in <7 days old infants) will be randomised to either outpatient care with injectable gentamicin for two days and oral amoxicillin for seven days (intervention) or inpatient care with injection gentamicin plus injection ampicillin along with supportive treatment, where needed, for seven days (control). We plan to enrol 7000 eligible young infants, 3500 infants in each of the two study arms. A trained and standardised independent outcome assessor will visit all enrolled cases on days two, four, eight and 15 post-randomisation to assess the study outcomes in both intervention and control groups. The primary outcome of poor clinical outcome, defined as death within two weeks of initiation of treatment, deterioration during the 7-day treatment period, or persistence of the presenting sign at the end of the 7-day treatment period, will be compared to assess if the outpatient treatment leads to superior or at least non-inferior clinical outcome than inpatient treatment. The selected sites have extensive research experience. The methods and all study procedures will be harmonised through central training of research staff by WHO, standardisation exercises for clinical signs, central data coordination centre and internal and external monitoring. Continuous evaluation of the enrolment by the sites will be carried out through regular calls, databased monitoring, and site visits by WHO monitors. This trial has received ethical approvals from the WHO and local site institutional ethics committees.

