## METHODS

### Research question

Among young infants, 0-59 days of age with only one low-mortality risk CSI sign presenting to the outpatient / emergency department of a hospital (population), does outpatient treatment with injectable gentamicin for two days and oral amoxicillin for seven days (intervention), compared to the currently recommended inpatient hospital treatment initiated with injectable ampicillin and gentamicin and supportive care for seven days (control), result in lower rates of poor clinical outcome (death within two weeks of initiation of treatment, deterioration during the 7-day treatment period, or persistence of the presenting sign of CSI at the end of the 7-day treatment period) (outcome)?

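### Table 3 prints two absolute non-inferiority margins, 1.8 and 1.5 percentage points, and the article does not say which one decides the non-inferiority conclusion

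*Protocol article*

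**What the plan says.** The abstract's Methods paragraph says that the primary outcome will be compared "to assess if the outpatient treatment leads to superior or at least non-inferior clinical outcome than inpatient treatment", and the Discussion describes the primary question in the same two-part way. Sample size states: "The sample size was calculated to test both the superiority and noninferiority hypotheses". It then gives the number: "The target enrolment is 7000 young infants (3500 in each study arm) with low-mortality risk signs". Allocation is equal: "Randomisation was in a 1:1 ratio".

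Table 3 has two superiority rows and two non-inferiority rows. The non-inferiority rows share the same risks, 6.0% in each arm, but differ in margin. One reads "Noninferiority 6.0 6.0 90% 1.8 5966". The other has 80% power, a margin of 1.5 and a total of 6202. The sentence before the table says that 7000 infants will meet the targets in it, and it ranks none of them. The column that holds the margins, "lower outcome or noninferiority margin", also holds the relative reductions of 30 and 25 for the superiority rows, and it gives the margins no unit of their own.

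Data analysis says only this about judging the comparison: "Risk difference and the 95% confidence intervals will be presented to assess". It repeats that the risk difference will have a 95% confidence interval, and it mentions no margin.

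**The concern.** The margin is the threshold that turns a confidence interval into a verdict. Two rows of a planning table may differ in power or in assumed event rate without changing what the trial concludes. Two rows that differ in margin can give opposite conclusions from the same data. The article promises a verdict on non-inferiority, prints two margins for it and does not say which governs. A reader holding the final interval could not always tell whether the trial met its stated aim.

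The result is meant to inform review of a guideline on hospitalising sick young infants, so that ambiguity matters if the upper limit lands between the two values.

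**Working it through.** **Inputs.** Control and outpatient risk 6.0% each; margins 1.8 and 1.5; power 90% and 80%; totals 5966 and 6202 (all Table 3). 3500 per arm (Sample size). 95% confidence interval of the risk difference (Data analysis). The significance level for the sample size is not stated, so it is inferred in step 1.

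**1. Reproduce the table.** For equal arms and unpooled variance, n per arm = (z_alpha + z_power)² × [p1(1−p1) + p2(1−p2)] / margin². The variance term is 2 × 0.06 × 0.94 = 0.1128.

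| Margin (points) | Power | Total at one-sided 5% | Total at one-sided 2.5% | Table 3 |
|---|---|---|---|---|
| 1.8 | 90% | (1.645 + 1.282)² × 0.1128 / 0.018² → 2982 per arm, 5964 | (1.960 + 1.282)² × 0.1128 / 0.018² → 3659 per arm, 7318 | 5966 |
| 1.5 | 80% | (1.645 + 0.842)² × 0.1128 / 0.015² → 3100 per arm, 6200 | (1.960 + 0.842)² × 0.1128 / 0.015² → 3935 per arm, 7870 | 6202 |

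The table is matched to within 2 infants at one-sided 5%. A restricted-variance score formula at the same level gives 6024 and 6252, which is close but further off. A continuity correction gives 6186 and 6464. No variant tried at one-sided 2.5% comes near.

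Two facts follow. The margins are absolute percentage points (30% and 25% of 6.0 are 1.8 and 1.5). The non-inferiority rows were planned at one-sided 5%, whereas the lower or upper limit of a two-sided 95% interval corresponds to one-sided 2.5%.

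**2. Where the two margins disagree.** At 3500 per arm and 6% risk, SE = √(0.1128 / 3500) = 0.568 points, and the 95% half-width is 1.96 × 0.568 = 1.11 points. The margins give different verdicts for observed differences (outpatient minus inpatient) from about 1.5 − 1.11 = 0.39 to 1.8 − 1.11 = 0.69 points.

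Example: 210/3500 (6.00%) inpatient and 228/3500 (6.51%) outpatient give +0.51 points, 95% CI −0.62 to +1.65. This is non-inferior at 1.8 and not at 1.5. With 210 inpatient events, any outpatient count from 224 to 233 splits in this way.

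**3. How likely a split is.** P(1.5 < upper limit < 1.8) = Φ((1.8 − D)/SE − 1.96) − Φ((1.5 − D)/SE − 1.96), where D is the true difference in points and SE is recomputed for each D.

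- D = 0: Φ(1.21) − Φ(0.68) = 0.887 − 0.752 = 13.5%
- D = +0.3 (SE 0.574): Φ(0.65) − Φ(0.13) = 19.1%
- D = +0.5 (SE 0.579): Φ(0.29) − Φ(−0.23) = 20.4%

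**4. Power with one margin, 3500 per arm, true difference 0, no losses.** Power = Φ(margin/SE − z_alpha).

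| Margin (points) | One-sided 5% | One-sided 2.5% (two-sided 95% CI) |
|---|---|---|
| 1.8 | 93.6% | 88.7% |
| 1.5 | 84.1% | 75.2% |

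**The case against.** The best counter-argument is that Table 3 is a power grid. Each design has one row at 90% and one at 80%, the title concerns sample size, and the text says only that 7000 is enough. On that reading no row is a decision rule. If both rows were binding, the stricter value would settle the matter, since a result that passes 1.5 also passes 1.8. This is a fair account of how the table probably arose. It does not remove the ambiguity, because the article never labels the rows as scenarios and never says that the stricter one governs.

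A second objection is that a condensed article commonly leaves the decision rule to the full protocol or SAP. That stands as far as it goes: silence on a margin in Data analysis would not be a finding on its own. What remains is that this article prints two margins and selects neither. A reader might infer that the margin can therefore be chosen after the data are seen. The article does not support that, because the documents not shown may already fix one.

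A third objection is that the 13% rests on a two-sided 95% interval, while the table used one-sided 5%. At the table's own level the split probability at a true difference of 0 is 93.6 − 84.1, or just under 10%. The dependence is real, but the 95% interval is the one the analysis section names.

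A reader might also see a conflict of hypotheses, since the research question asks only whether outpatient care would "result in lower rates of poor clinical outcome". The abstract, Sample size and Discussion all state both hypotheses, so this is a matter of aligning wording.

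**Conclusion.** The concern holds in a limited form. The article states two absolute non-inferiority margins, presents both as targets and does not say which decides the conclusion it promises. The chance of a result on which they disagree is about 13% at a true difference of 0 and about 20% at +0.5 points. These figures assume 3500 evaluable infants per arm, 6% control risk, a normal approximation and a two-sided 95% interval.

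A linked point emerges from the reproduction: the power quoted in the non-inferiority rows belongs to a one-sided 5% test and is not what the 95% interval delivers. The level is inferred from the arithmetic because the article does not state it. This does not show that 7000 is an inadequate target. It shows that 90% and 80% overstate the power for the interval named in Data analysis.

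**What to change.** Before any comparative data are seen, name one margin, in absolute percentage points, as the decision threshold in both Sample size and Data analysis. State the rule beside it: outpatient care is non-inferior if the upper limit of the two-sided 95% confidence interval for outpatient minus inpatient risk is below that margin, and superior if that limit is below 0. The other row may stay if it is labelled as a scenario. If the full protocol or SAP already names a margin, quote it.

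Restate the power for the chosen margin at the level of that interval. With 7000 infants and no losses it is 88.7% for 1.8 points or 75.2% for 1.5 points; any losses lower it further. Keeping the table's 90% or 80% at that level would need 7318 or 7870 infants.

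The change is to wording only. Its cost is a slightly less favourable stated power, and the trial team should choose the margin with those two figures in view.

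### Table 3, first superiority row: 6.0% to 4.0% is a 33% reduction needing about 4980 infants; the printed 30% and 6270 belong to 6.0% to 4.2%

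*Protocol article*

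**What the plan says.** The Sample size section of the protocol article sets a target of 7000 infants, 3500 per arm, and supports it with Table 3: "This sample size will allow us to meet the superiority and inferiority targets". The table has two superiority rows and two noninferiority rows.

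- First superiority row: "Superiority 6.0 4.0 90% 30 6270".
- Second superiority row: "Superiority 6.0 4.5 80% 25 6938".

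The column that holds 30 and 25 is headed as the percentage "lower outcome or noninferiority margin". In the second row, 25 is the relative reduction from 6.0 to 4.5, so for superiority rows the column means relative reduction.

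The section states no alpha, sidedness or dropout allowance. Elsewhere the article says "Randomisation was in a 1:1 ratio" (Randomisation to treatment arms) and "Risk difference and the 95% confidence intervals will be presented" (Data analysis).

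**The concern.** The first superiority row gives the same effect twice, once as a pair of risks and once as a relative reduction, and the two versions differ. The sample size can belong to only one of them.

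This row is one of the targets that the protocol says its enrolment will meet. A reader who takes the printed risks at face value concludes that 6270 infants give 90% power for an absolute difference of 2.0 points. If the 30% and the 6270 are what was calculated, the difference is 1.8 points. Nobody can reproduce the row as it stands, and anyone who reuses it carries one version or the other forward.

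**Working it through.** **Inputs.** Risks, powers, reductions and totals come from Table 3; 1:1 allocation comes from Randomisation to treatment arms. Two-sided alpha of 5% is an assumption. It agrees with the planned 95% confidence intervals and is tested in step 2. No dropout inflation is applied.

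**Step 1: relative reduction (no assumption needed).**

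- Second row: (6.0 − 4.5)/6.0 = 25.0%, as printed.
- First row: (6.0 − 4.0)/6.0 = 33.3%, printed as 30.
- A 30% reduction: 6.0 × (1 − 0.30) = 4.2.

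**Step 2: calibrate on the second superiority row.** With d = p1 − p2 and p̄ the mean of the two risks, the number per arm is:

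- unpooled: (z_α/2 + z_β)² × (p1q1 + p2q2) / d²
- pooled: [z_α/2 √(2p̄q̄) + z_β √(p1q1 + p2q2)]² / d²

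For 6.0% versus 4.5% at 80% power, unpooled: (1.960 + 0.842)² × (0.0564 + 0.042975) / 0.015² = 3466.6 per arm, total 6934 after rounding each arm up. Pooled: total 6940. The table prints 6938, so the method and the assumed alpha reproduce this row.

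**Step 3: apply the same method to the first row at 90% power.**

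- 6.0% versus 4.0%, unpooled: (1.960 + 1.282)² × (0.0564 + 0.0384) / 0.020² = 2490.3 per arm, total 4982.
- 6.0% versus 4.2%, unpooled: (1.960 + 1.282)² × (0.0564 + 0.040236) / 0.018² = 3133.9 per arm, total 6268.

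| Comparison, power | Unpooled total | Pooled total | Printed total |
|---|---|---|---|
| 6.0 vs 4.5, 80% | 6934 | 6940 | 6938 |
| 6.0 vs 4.0, 90% | 4982 | 4988 | 6270 |
| 6.0 vs 4.2, 90% | 6268 | 6276 | 6270 |

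As printed, 6270 exceeds what 6.0% versus 4.0% needs by 6270 − 4988 = 1282 to 6270 − 4982 = 1288 infants, about 20% of the printed figure. With 4.2% the printed figure is matched within 0.1%.

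**Step 4: power at the stated sizes.** Power = Φ{[d − 1.960 √(2p̄q̄/n)] / √[(p1q1 + p2q2)/n]}.

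| Total (per arm) | 6.0 vs 4.0 | 6.0 vs 4.2 |
|---|---|---|
| 6270 (3135) | 95.3% | 90.0% |
| 7000 (3500) | 97.0% | 92.8% |

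**Step 5: could another setting rescue 6.0% versus 4.0%?** The pooled formula was rerun under other settings, and each was also applied to the second row (printed 6938).

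| Setting | 6.0 vs 4.0, 90% (printed 6270) | 6.0 vs 4.5, 80% (printed 6938) |
|---|---|---|
| One-sided 5% | 4066 | 5466 |
| Two-sided 5%, continuity correction | 5186 | 7204 |
| Two-sided 2.5% | 5892 | 8404 |
| Two-sided 2.5%, continuity correction | 6090 | 8668 |
| One-sided 1% | 6180 | 8874 |
| Two-sided 1% | 7064 | 10326 |
| Two-sided 5%, 20% dropout | 4988/0.8 = 6235 | 6940/0.8 = 8675 |

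The arcsine formula at two-sided 5% gives 4944 and 6908. Some settings come near 6270 for the first row, but every one of those misses the second row by a wide margin. None of them turns 33% into 30%.

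**The case against.** The strongest case on the other side is that nothing in the trial changes.

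- **The row does not drive enrolment.** The second superiority row, at 6938, sets the 7000, and it is correct. At 7000 the 90% target is exceeded under either reading, so the claim that the targets are met survives for this row. This stands.
- **The error is in the safe direction.** For the printed risks, 6270 is a surplus and 90% understates the power. This also stands; no shortfall is alleged.
- **4.2% is an inference.** The table gives no absolute difference for superiority rows, so 1.8 points follows only if 4.2% was intended. That is right, and the authors should confirm it. Still, two entries (30 and 6270) agree on 4.2% and only one disagrees. Rounding to whole numbers is no explanation, because the column carries one decimal and shows 4.5 in the next row.
- **Alpha is not given and is not uniform across the table.** The noninferiority rows (5966 and 6202) reproduce at one-sided 5% (5964 and 6200), not at one-sided 2.5% (7318 and 7870). The figure of about 4980 is therefore conditional on two-sided 5%. At one-sided 5% the first row would need only 4066, further still from 6270. The mismatch between 33% and 30% depends on no alpha at all.

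These points limit the consequence of the error. None of them reconciles the row, and nothing else in the article corrects it.

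**Conclusion.** The row is wrong as written. That the relative reduction contradicts the two risks is certain and needs no assumption. That the sample size also contradicts them rests on two-sided 5%, 1:1 allocation and no dropout inflation, which together reproduce the neighbouring superiority row. On that basis 6270 is about 1,285 infants more than the printed effect needs, and it fits 6.0% versus 4.2% within 0.1%. The likeliest explanation is a single wrong cell, 4.0 in place of 4.2. This is a correction to a stated design target. It does not affect the enrolment target or the attainability of 90% power.

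**What to change.** Check the original calculation, then make the row agree with itself:

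1. If the 30% reduction was intended, which the evidence favours, change the intervention risk from 4.0 to 4.2 and keep 90%, 30 and 6270.
2. If 4.0% was intended, change 30 to 33 and 6270 to about 4980.

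In either case, state alpha and sidedness beside Table 3, separately for the superiority and noninferiority rows, so that each row can be reproduced. The cost is one table cell (two under the second option) and a short note. The target of 7000 stays as it is.
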